
The self-expandable COMPLETE-SE™ stent has three distinct crown configurations, and an alternating connection pattern minimizes crown-to-crown interaction and provides optimal flexibility, foreshortening, and lesion coverage for each stent size. The triaxial deployment design includes an inner shaft, a retractable sheath, and a stabilizing sheath, which reduces friction and allows the retractable sheath to move back freely. This decreases the amount of force required to deploy the stent, making deployment easy and accurate. Diameter and length of self-expandable COMPLETE-SE™ stents are 5–10 mm and 20, 40, 60, 80, 100, 120, and 150 mm, respectively. Balloon-expandable SCUBA stents are composed of thin cobalt-chromium struts, unlike other stainless steel stents, and have a closed-cell design for tight scaffolding and appropriate radial strength in iliac lesions. Diameter and length of balloon-expandable SCUBA™ stents are 6–10 mm and 20, 30, 40, and 60 mm, respectively. The entire stent size (the COMPLETE-SE™ and SCUBA™ stent) is now 6-Fr sheath compatible. We will use either a 0.035” or 0.018” wire system and implant either a SCUBA™ or COMPLETE-SE™ stent. All ipsilateral femoropopliteal arterial lesions should be treated with angioplasty and/or stenting concomitantly and residual stenosis should be less than 50 %. Treatment of tibioperoneal lesions is recommended only in cases of CLI. There should exist at least one patent (<50 % stenosis) tibioperoneal run-off vessel with good antegrade flow. A final angiography will be performed after the intervention in both groups, with the use of the same angles and magnifications used at the baseline angiograms. Simultaneously, reference vessel diameter (RVD), minimal luminal diameter (MLD), percent diameter stenosis, and acute gain should be measured. The RVD will be obtained from averaging 5-mm segments proximal and distal to the lesion. Technical success will be defined as successful access, deployment of the stent, and less than 30 % diameter residual stenosis after the revascularization. For postprocedural medication, aspirin 100 mg and clopidogrel 75 mg will be administered once daily for at least 12 months. Cilostazol would be permitted as the third antiplatelet at the physician’s discretion. After enrollment and index procedure, clinical follow-up will be planned at 1, 6, and 12 months to evaluate clinical outcomes and ankle-brachial index (ABI) score. In addition, a follow-up catheter angiography, CT angiography, or duplex ultrasound will be recommended to all patients at 12 months, according to local clinical practice. The investigators will be urged to follow up on patients, either by office visits or by telephone contacts, as necessary. Patient adherence to the study drug and side effects will be checked and monitored at every outpatient visit. The decision of drug discontinuation will be discussed and checked at the physician’s recommendation.

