#### Sample size calculation

Although patency definitions varied across trials, 1-year patency rates in aortoiliac lesions were approximately 90 % on average from previous studies including CRISP-US and MELODIE [22, 23]. In the case of the SCUBA™ stent, the 9-month patency rate for the SCUBA™ stent was 99.2 % in the ACTIVE study - a prospective, multicenter, single-arm study that defines the midterm efficacy of a next-generation cobalt-chromium iliac stent for the treatment of de novo and restenotic lesions in iliac arteries [25]. However, a different definition - a ratio of <2.4 between the duplex peak systolic velocity in the treated vessel segment and the reference systolic velocity - was used, unlike the more common definition. There are limited data on the 1-year primary patency rate of the SCUBA™ stent. Based on the MELODIE trial [23], and the European multicenter iliac stent trial [26], the 1-year primary patency of the SCUBA™ stent was estimated to be 88 %, and the COMPLETE-SE™ stent was estimated to be 94.7 % in the CRISP-US trial. Therefore, the self-expandable COMPLETE-SE™ stent group will be the control group, and the balloon-expandable SCUBA™ stent group will be the experimental group.

Patency rate will be defined as absence of occlusion and absence of >50 % stenosis in the treated segment by quantitative coronary angiography (QCA) or if invasive angiography is not performed, PSVR ≤2.5 when evaluated with duplex ultrasound. On the basis of previous studies [22, 23], we hypothesize that the expected patency rate after stent deployment at 1 year would be 90 % for the self-expandable stent group, and 88 % for the balloon-expandable stent group, respectively. The predetermined noninferiority margin δ is a 10 % difference between treatment groups. There was clinical consensus that this noninferiority margin would be acceptable if safety is maintained and patients are treated more easily, regardless of stent classification. The power analysis is based on a noninferiority principle. The statistical significance level is 2.5 % at one side, the power of the test is set as 80 %, and the randomization ratio is set as 1:1. The test for proportion and the chi-square method will be used. Using standard sample size formula, it was calculated that 120 patients per group are needed for a total of 288 patients, after accounting for a 20 % dropout rate.

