### Statistical analysis

The IBM SPSS 20.0 (IBM Corp., Armonk, NY, USA) statistics program will be used for all analysis. Categorical variables will be expressed as delivery rate when comparing baseline features between the SCUBA™ and COMPLETE-SE™ stent groups and for categorical variables, comparisons between groups will use the chi-square or Fisher’s exact test. Continuous variables will be expressed as mean ± standard deviation, and for continuous variables, comparisons between groups will use the Student’s *t* test. The primary and secondary end points will be analyzed using both intention-to-treat analysis (all subjects assigned to a treatment group) and per protocol analysis (only subjects who completed the treatment protocol). Noninferiority will be considered proven if conclusions drawn from the intention-to-treat and per protocol analyses are consistent. Balloon-expandable stent patency will be judged as noninferior to that of the self-expandable stent when the lower limit of the 95 % CI of the difference between the proportions of patent patients at 1 year in both groups is higher than -δ = −10 % At the end of the 12 months, cumulative restenosis rates will be calculated. For a secondary end point, we will summarize with descriptive statistics and compare between treatment groups using the Student’s *t* test, chi-square test, or Fisher’s exact test. Also, clinical outcomes such as revascularization of the target vessel, death, major cardiovascular events including myocardial infarction and cerebral infarction, and limb salvage rates will be analyzed using Kaplan-Meier survival estimates and a comparison of the groups will be performed using the log-rank test. A *P* value <0.05 will be considered to be statistically significant. In order to evaluate the risk factors for recurrence, defined as restenosis or total occlusion, univariate and multivariate logistic regression analysis will be performed. The present research has concluded that there will be a very low chance of missing data to cause bias, and therefore, missing data for the major end points will be excluded from the analysis data.

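### Patients without a 12-month patency result are excluded, so the intention-to-treat noninferiority result is a complete-case result with no safeguard against informative missingness

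*Protocol article*

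**What the plan says.** Five statements in the protocol article bear on this point.

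- Statistical analysis, handling of missing outcomes: "missing data for the major end points will be excluded from the analysis data". The reason given is that "there will be a very low chance of missing data to cause bias". The article gives no supporting figure and names no sensitivity analysis.
- Statistical analysis, analysis sets: the end points are analysed by "intention-to-treat analysis (all subjects assigned to a treatment group") and also per protocol, among those who completed the treatment protocol. Noninferiority needs consistent conclusions from both.
- Sample size calculation: "120 patients per group are needed for a total of 288 patients, after accounting for a 20 % dropout rate".
- Randomization and interventions: catheter angiography, CT angiography or duplex ultrasound "will be recommended to all patients at 12 months, according to local clinical practice". Follow-up contact may be by office visit or telephone.
- The same section lets the principal investigator withdraw patients for protocol violations or because they are no longer treated at a participating hospital. It warns that too many withdrawals could make the study uninterpretable.

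**The concern.** Patency is defined by imaging in Outcome measures, Sample size calculation and the Appendix. A patient without a 12-month image therefore has no primary outcome unless some other rule supplies one, and the exclusion rule removes that patient. The analysis then covers only allocated patients with an observed outcome, which is not the intention-to-treat set that the article defines.

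Requiring agreement between the two analyses does not repair this, because both omit the same unobserved patients. If the omission distorts the difference, it distorts both in a similar way.

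The article also does not say how an occlusion, restenosis or target lesion revascularization (TLR) documented before month 12 counts when there is no month-12 scan. Under the exclusion rule, some known failures may leave the analysis.

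At stake is the error rate of the primary claim. Whether a patient is imaged under local practice may depend on symptoms, on withdrawal, or on which stent was placed. If failures are lost more often than patent cases, the observed difference can shrink and noninferiority can be declared when the true loss of patency equals the margin.

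**Working it through.** **The plan's own figure.** 2 × 120 × 1.2 = 288, so 144 per arm; the stated total is reproduced from the stated 120. Whether 120 follows from the power inputs is a separate matter and is not used here. The Abstract's total of 280 would give 140 per arm and barely changes the results.

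**Loss.** 20% of 144 = 28.8, about 29 per arm and 58 in all, leaving about 115 per arm.

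**Inputs from the documents.** Margin 10 points; noninferiority if the lower 95% limit exceeds −10 points; expected self-expandable patency 90%.

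**Assumptions.** True balloon-expandable patency of 80%, which puts the true difference exactly at the margin, and every missingness pattern below.

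**Formula.** Let q be observed patency among complete cases (S self-expandable, B balloon-expandable) and d = q_B − q_S. Then SE = √[q_S(1−q_S)/n_S + q_B(1−q_B)/n_B], and the false noninferiority rate = Φ[(0.10 + d)/SE − 1.96]. With d = −0.10 this is Φ(−1.96) = 2.5%.

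**Model 1: missing patients have patency g below observed ones, balloon-expandable arm only.** 0.80 = 0.8q_B + 0.2(q_B − g), so q_B = 0.80 + 0.2g; q_S = 0.90; n = 115 per arm.

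| g | q_B | d | SE | False noninferiority |
|---|---|---|---|---|
| 0.09 | 0.818 | −0.082 | 0.0456 | 5.9% |
| 0.18 | 0.836 | −0.064 | 0.0444 | 12.5% |
| 0.27 | 0.854 | −0.046 | 0.0432 | 23.9% |

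With the same g in both arms, q_S = 0.90 + 0.2g. Then d stays at −0.10 and the rate at 2.5%.

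**Model 2: a fraction a of patent cases and b of failures is lost.** For true patency p, q = p(1−a)/[p(1−a) + (1−p)(1−b)], and n = 144 × that denominator. Overall loss is about 20% per arm in each row; a/b is shown in percent.

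| S: a/b | B: a/b | q_S | q_B | d (points) | False noninferiority |
|---|---|---|---|---|---|
| 20/20 | 20/20 | 90.0% | 80.0% | −10.0 | 2.5% |
| 16.7/40 | 16.7/40 | 92.6% | 84.7% | −7.8 | 7.5% |
| 15/50 | 15/50 | 93.9% | 87.2% | −6.7 | 13.6% |
| 20/20 | 17.5/30 | 90.0% | 82.5% | −7.5 | 8.0% |
| 20/20 | 15/40 | 90.0% | 85.0% | −5.0 | 20.9% |
| 17.8/40 | 20/20 | 92.5% | 80.0% | −12.5 | 0.6% |
| 21/10 | 21/10 | 88.8% | 77.8% | −10.9 | 1.6% |
| 20/20 | 22.5/10 | 90.0% | 77.5% | −12.5 | 0.7% |

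A simulation of 200,000 trials per scenario (144 per arm, Wald interval) gives slightly higher rates: 2.8%, 8.6%, 15.4%, 8.7% and 22.0% for the first five rows, and 0.7% for the sixth.

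**How fragile one result is.** Suppose 104 of 115 are patent in each arm.

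- Complete cases: difference 0, 95% CI −7.6 to +7.6 points, noninferior.
- Set the 29 missing controls at the observed rate: 104/115 × 144 ≈ 130 of 144. Of the 29 missing balloon-expandable patients, let k be failures, giving (104 + 29 − k)/144. With k = 6 (127/144) the lower limit is −9.2. With k = 7 (126/144) it is −10.03, and noninferiority is lost.
- The conclusion therefore turns at 7/29 = 24% failures among the missing, against 11/115 = 9.6% among the observed.

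**The case against.** The strongest reply is that the bias has no fixed direction. If patients with symptoms are the ones who get imaged, the unimaged do better. Complete-case analysis then exaggerates the deficit and false noninferiority falls below 2.5% (the last two rows of Model 2). Losing mainly control failures does the same, and an equal gap in both arms leaves the difference untouched. This stands: the inflated rates are possibilities under assumptions, not predictions.

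Four stronger readings are tempting, and the documents do not support them.

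- **The plan discards known failures.** The rule concerns missing data. Patency is also described as absence of occlusion and of more than 50% stenosis, and cumulative restenosis rates are planned, so a documented early occlusion is not plainly missing. The text is silent on this, and may exclude is as far as one can go.
- **Agreement of the two analyses is worthless.** It still addresses deviations from the treatment protocol. It is weak only against missing outcomes.
- **The 20% allowance contradicts the reassurance.** The reassurance is about bias, and the 20% is a planning allowance for quantity. The reassurance is unsupported rather than contradicted.
- **Imaging depends on knowledge of the stent.** The article does not say who was blinded or who reads the images, so this is a plausible route and not a documented one.

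One cannot answer that the matter was left to an analysis plan. The article states the exclusion rule and its justification outright.

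**Conclusion.** The point holds. As written, the primary intention-to-treat analysis is a complete-case analysis that conflicts with its own definition. It rests on an unsupported statement about bias, and the second analysis set gives little protection against that bias.

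Assuming about 20% missing per arm and a true 90% versus 80%, the nominal 2.5% error becomes:

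- 2.5% if loss is completely at random or the gap is equal in both arms;
- about 7–14% if failures are lost more often by the same mechanism in both arms;
- about 6–24% if loss is informative only in the balloon-expandable arm, with failures lost more often;
- about 0.6–1.6% if failures are lost less often than patent cases, or if mainly control failures are lost.

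A reader might infer that exclusion will produce false noninferiority. The documents support only that it can, and that nothing in the stated analysis would reveal it. Because the rule governs the primary claim, it should be changed before the analysis.

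**What to change.** Replace the exclusion rule in Statistical analysis with the following.

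1. The primary intention-to-treat analysis keeps every randomised patient.
2. Occlusion or restenosis documented before month 12 counts as not patent, with or without a month-12 scan. State explicitly that TLR before month 12 also counts as loss of primary patency, and label this a clarification of the end point, since the current definitions rest on imaging alone.
3. State in advance how deaths before month 12 without a patency assessment are handled, so that they are not imputed by default.
4. Multiply impute the remaining missing outcomes by arm, using baseline data and the ankle-brachial index and Rutherford follow-up.
5. Add a tipping-point analysis that progressively worsens imputed patency in the balloon-expandable arm.
6. Keep the complete-case analysis as a sensitivity analysis. Counting all missing patients as failures in both arms should not be the only alternative, because it can pull the arms together.

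The cost is analysis-plan wording, modest programming and a slightly wider confidence interval.

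Requiring one of the three listed imaging modalities at 12 months would reduce the problem at its source. In a trial that is still recruiting, that is a separate, optional protocol and site-conduct amendment with its own cost. The analysis fix does not depend on it.

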### Trial organization

#### Executive committee

The Executive Committee will be composed of the study chairperson and selected members among the investigators. This committee is responsible for overseeing the administrative progress of the study and will approve the final trial design and protocol issued to the Data and Safety Monitoring Board (DSMB) and the clinical sites. This committee will also be responsible for reviewing the final results, determining the methods of presentation and publication, and selection of secondary projects and publications by members of the Steering Committee. The Executive Committee also holds the right to modify or stop the study prematurely based on recommendations from the DSMB.

#### Data Safety Monitoring Board (DSMB)

The frequency of the DSMB meetings will be determined prior to study commencement. Additionally, the DSMB may call a meeting at any time if there is reason to suspect that safety is an issue. The DSMB is responsible for making recommendations regarding any safety or compliance issues throughout the course of the study and may recommend to the Executive Committee to modify or stop the study. However, all final decisions regarding study modifications rest with the Executive Committee. All cumulative safety data will be reported to the DSMB and reviewed on an ongoing basis throughout enrollment and follow-up periods to ensure patient safety. Every effort will be made to allow the DSMB to conduct an unbiased review of patient safety information. All DSMB reports will be made available to the appropriate agencies upon request, but will otherwise remain strictly confidential. Prior to the DSMB’s first review of the data, the DSMB charter will be drafted. The DSMB will develop a consensus understanding of all trial end points and definitions used in the event of an adjudication process. All DSMB reports will remain strictly confidential, but will be made available to the regulatory body upon request.

#### Clinical Event Adjudication Committee (CEAC)

The Clinical Event Adjudication Committee (CEAC) is comprised of interventional and noninterventional cardiologists who are not involved in the study. The CEAC is charged with the development of specific criteria used for the categorization of clinical events and clinical end points in the study, which are based on protocol. At the onset of the trial, the CEAC will establish explicit rules outlining the minimum amount of data required and the algorithm to be followed in order to classify a clinical event. All members of the CEAC will be blinded to the primary results of the trial. The CEAC will meet regularly to review and adjudicate all clinical events. The CEAC will also review and rule on all deaths that occur throughout the trial.

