## Method/design

### Study objectives, hypothesis, and design

The primary purpose of our study is to compare primary patency between self-expandable nitinol stents and balloon-expandable cobalt-chromium stents in real-world clinical practice (COMPLETE-SE™ versus SCUBA™, Medtronic, Minneapolis, MN, USA) in stenotic or occlusive iliac arterial lesions. The secondary purpose is to ascertain whether there is a difference in safety, including the incidence of geographic miss rate and stent fracture rate between both groups in patients undergoing stent implantation in iliac lesions. This is a prospective, randomized, multicenter trial to assess the efficacy and safety of the COMPLETE-SE™ versus the SCUBA™ stent by provisional stenting after balloon angioplasty for steno-occlusive iliac arterial lesions. A description of this manuscript according to the SPIRIT guidelines is presented in Additional file 1

The protocol of the trial has been registered with the National Institutes of Health Clinical Trials Registry (registration number: NCT01834495) and a brief flow chart of the whole study is summarized in Fig. 1.

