### Randomization and interventions

Prior to the endovascular intervention, informed consent (see Additional file 2) will be obtained from all participants by investigators. Aspirin and clopidogrel will be administered at least 12 hours before the procedure. Prior to the intervention, 70 to 100 units/kg of unfractionated heparin will be administered. Endovascular interventions will be carried out percutaneously, by placing a 6–8Fr sheath at the femoral artery via an antegrade approach or a contralateral crossover technique. In selected cases, a retrograde approach (from the distal superficial femoral artery (SFA), popliteal artery, or pedal arteries) and/or brachial approach will be allowed. Diagnostic angiography will be performed in two different views at least 30 to 45° apart to evaluate the structure of the target lesion. Femoropopliteal and tibial arteries will be visually checked for the presence of distal lesions. To document the precise location of the lesion and the site of the intervention, we will recommend the use of a ruler. In cases of total occlusion, both intraluminal and subintimal methods of recanalization will be allowed. During the procedure, the use of other special devices will be allowed; for example reentry devices OUTBACK™ catheters (Cordis Corp., Miami Lakes, FL, USA) and Offroad catheters (Boston Scientific, Natick, MA, USA), chronic total occlusion (CTO) devices Frontrunner (Cordis Corp., Miami Lakes, FL, USA) and Truepath (Boston Scientific, Natick, MA, USA), and atherectomy devices such as SilverHawk™ and TurboHawk™ (Covidien, Plymouth, MN, USA). After the successful passage of the guidewire, predilation of the target lesion with an optimally sized balloon will be performed prior to stent implantation. Recommended minimal balloon dilation time is 120 seconds. Then, if there is a residual pressure gradient of ≥10 mmHg, residual stenosis of ≥30 %, or flow-limiting dissection, the balloon angioplasty results will be considered as suboptimal results. Subsequently, web-based randomization for stent selection will be performed. Patients will be randomly allocated to one of two groups, the balloon-expandable or self-expandable stent group, according to the stent deployment method. Random allocation of the patients will be performed via a web-based computerized program separately managed at the Cardiovascular Intervention Research Institute (CIRI), Korea University Guro Hospital, Seoul, Republic of Korea. Patients will be randomized in a 1:1 manner according to two different stents (SCUBA™ versus COMPLETE-SE™). The stents will be implanted to extend 10 mm proximally and distally from the margins of the target lesion with luminal narrowing of ≥50 %. A proper stent size will be selected after review of the baseline angiography results. If the stent is randomized to the COMPLETE-SE™, a stent with a diameter 1 to 2 mm larger than that of the true vessel lumen will be selected. However, if the stent is randomized to the SCUBA™ stent, a stent of equal size to the reference vessel diameter will be selected to prevent iliac artery injury. Spot stenting or full lesion coverage will be decided at the physician’s discretion. When multiple stents are required, the margins of the stents should be overlapped by at least 10 mm. Adjuvant postdilation after the stenting will be performed strictly within the stented segment, with up to 10 % oversizing of the postdilation balloon.

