## Appendix

### 1. End points definitions

- Primary patency: defined as stenosis of at least 50 % of the luminal diameter according to the worst angiographic view at the narrowest site within the treated segment plus the 10-mm segments proximal and distal to the treated segment by catheter angiography or CT angiography; PSVR ≥2.5 (PSVR = peak systolic velocity within the area of stenosis divided by peak systolic velocity in a normal adjacent proximal artery segment) or total occlusion by duplex ultrasound
- Geographic miss according miss grade (mild, moderate, severe): geographic miss is classified as 5–15 mm (mild), 15–25 mm (moderate), >25 mm (severe), or additional stent deployment over the stent deployment area that was not covered, or protrusion from the intended stent deployment area
- Stent fracture rate according fracture grade (minor, moderate, severe), [28] plain X-ray examinations for the stent fracture are used or performed using at least two different angulations (30 to 45° difference) and the highest available magnification. Stent fracture is classified as minor (single strut fracture), moderate (fracture of more than two struts), or severe (complete separation of stent segments)
- Target lesion revascularization (TLR): defined as any repeat percutaneous intervention of the target lesion or bypass surgery of the target vessel performed for restenosis because of a return of ischemic symptoms, decrease of at least one Rutherford category, decrease in the ankle brachial index of >0.15, or restenosis of >50 % as measured by catheter angiography. The target lesion is defined as the treated segment from 10 mm proximal to the stent and to 10 mm distal to the stent
- Target extremity revascularization (TER): defined as any repeat percutaneous intervention of the target extremity or bypass surgery of the target extremity performed for restenosis because of a return of ischemic symptoms, decrease of at least one Rutherford category, decrease in the ankle brachial index of >0.15, or restenosis of >50 % as measured by catheter angiography
- Limb salvage: defined as survival free of amputation. Amputation is defined as above-ankle amputation of the index limb

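### The event committee is blinded to the trial's primary results, not to the assigned stent, so adjudication of the judgement-based secondary end points is not stated to be masked to allocation

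*Protocol article*

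**What the plan says.** The CEAC section of the protocol article describes a committee of "interventional and noninterventional cardiologists who are not involved in the study". It gives the committee its task: "The CEAC will meet regularly to review and adjudicate all clinical events". It also says that at the start of the trial "the CEAC will establish explicit rules outlining the minimum amount of data required and the algorithm to be followed". The committee rules on all deaths as well. The one sentence on blinding reads "All members of the CEAC will be blinded to the primary results of the trial".

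The design statement names no masking and does not use the term open-label: "This is a prospective, randomized, multicenter trial to assess the efficacy and safety of the COMPLETE-SE™ versus the SCUBA™ stent". Under Randomization and interventions, allocation takes place during the procedure, and the sizing rule depends on the result: "If the stent is randomized to the COMPLETE-SE™, a stent with a diameter 1 to 2 mm larger than that of the true vessel lumen". The SCUBA arm has a different sizing rule.

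Among the events, Appendix section 1 defines TLR as a repeat procedure "performed for restenosis because of a return of ischemic symptoms, decrease of at least one Rutherford category", with an ankle-brachial index fall above 0.15 or angiographic restenosis above 50 % as further alternatives. TER is worded in the same way for the whole extremity.

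**The concern.** When the person placing the device cannot be blinded, the usual protection for clinical events is a committee that classifies them without knowing the treatment. Here the article states a blinding rule for that committee, but the rule names something other than the treatment. An adjudicator can comply with it fully and still know the stent in every case.

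This matters where classification needs judgement: whether a repeat procedure was done for restenosis with returning symptoms, or whether an episode counts as a myocardial infarction or a stroke. The Background says the choice between the two stent types now rests mainly on operator preference, and the committee includes interventional cardiologists, so prior views about stent type are plausible. Such views could move borderline calls in either direction.

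**Working it through.** The point concerns a rule, not a figure, so the check is a comparison of sections.

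**1. Who knows the stent.** The operator does, by necessity: the stent is drawn during the procedure and sized by a stent-specific rule (Randomization and interventions). That the trial is open at the operator level is an inference from this section, but a secure one.

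**2. Who is masked to the stent.** The whole article was checked for blinding, masking, open-label, core laboratory and adjudication. No section masks patients, follow-up assessors, image readers or the CEAC to allocation. The section on the Data Safety Monitoring Board speaks of an unbiased safety review but says nothing of masking adjudicators.

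**3. What the stated rule can achieve, on each reading of primary results.**
- *The comparative 12-month result.* It does not exist in final form while the committee is meeting regularly to classify events, and withholding it does not hide the stent.
- *Patency findings as they accrue, patient by patient.* Withholding these has some purpose, but the stent remains visible. It would also sit awkwardly with the TLR and TER definitions, which use angiographic restenosis as one criterion.
- *Loose wording for allocation.* The intention would then be right, but the sentence does not say so and needs correcting.

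On the first two readings the stent is not masked. On the third, the text must change.

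**4. Which end points are exposed.**

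| End point | Judgement in classification | Exposed to knowledge of stent |
|---|---|---|
| TLR, TER | Partly: symptoms and the reason for the procedure; ankle-brachial index and percent restenosis are measured | Yes, in part |
| Myocardial infarction, stroke | Yes | Yes |
| MACE | Through its components | Through myocardial infarction and stroke; through TLR only under the Appendix definition, since Outcome measures lists repeat coronary intervention instead |
| All-cause death | Practically none | Not shown |
| Primary patency at 12 months | Read on angiography, CT or duplex; the reading is not assigned to the CEAC | Not shown |

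**5. Scale, as arithmetic only.** The article gives no expected rate for these end points in this trial. The only revascularization rates it cites are 2.0 % and 4.0 % at 9 months, from the earlier randomized comparison of two self-expanding stents (Background). Carried over as an assumption to 120 patients per arm, they give 120 × 0.020 = 2.4 and 120 × 0.040 = 4.8 events. With 288/2 = 144 per arm they give 144 × 0.020 = 2.9 and 144 × 0.040 = 5.8. Reclassifying one event moves an arm's rate by 1/120 = 0.8 or 1/144 = 0.7 percentage points. Two events move it by 2/120 = 1.7 or 2/144 = 1.4 points. This shows how few calls make up such a rate. It says nothing about how likely a biased call is.

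**The case against.** The strongest reply is that the article does not say adjudicators will know the stent. It gives one blinding rule and is otherwise silent, and the contents of event packets are commonly left to a fuller protocol or a committee charter, neither of which is shown. This stands as a limit: one cannot conclude that adjudication will in fact be unmasked. It does not remove the point, because the article chose to state the rule and named an object that does not serve the purpose.

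Second, protection already exists. Adjudicators come from outside the study and work to an algorithm fixed at the start. Two of the TLR and TER criteria are measurements, meeting any one criterion is enough, and whether a repeat procedure took place is a fact. This lowers the risk, but independence is not masking and rules do not settle every borderline case.

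Third, much of the open-label risk for TLR and TER lies in the treating physician's decision to reintervene, which no committee blinding changes. This stands in full.

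A reader might also infer that the noninferiority conclusion is at risk. The documents do not support that. The 10 % margin and the decision rule apply only to 12-month patency. Secondary end points are compared by ordinary tests with no margin. The sample size section does make the margin's acceptability conditional on safety being maintained, but it sets no formal test for that. Nor does the committee's ruling on deaths add to the concern: both MACE definitions count death from any cause, and the Statistical analysis section does not split death by cause.

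**Conclusion.** The concern holds for the secondary clinical end points that need judgement: TLR, TER, myocardial infarction, stroke, and MACE through these. For them the article states a blinding rule that leaves the assigned stent visible, and nothing elsewhere supplies the missing masking. Independence and pre-set rules reduce the exposure without removing it.

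The documents show no effect on all-cause death or on the primary patency analysis. Neither the size nor the direction of any bias can be estimated from them. The verdict rests on taking the blinding sentence as written and on the inference that the operator knows the stent. If a charter not shown here already masks the committee to allocation, only the article's sentence needs correcting. This is an inexpensive improvement to the plan, not a threat to its main conclusion.

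**What to change.** Reword the CEAC sentence to say that members are blinded to stent allocation. Have the existing data-coordination staff remove stent name and type from event packets, and have the committee work from redacted narratives and reports first, opening images only where a case cannot be classified without them.

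The cost is one sentence and routine redaction; sample size, treatment and visits are unchanged. The article reports the trial as still recruiting, so the change could still reach events not yet adjudicated. Two limits remain: masking is incomplete whenever an image showing the stent must be viewed, and the decision to reintervene is still made by a physician who may know the stent.
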